## 7.10 Modification of trial treatment

For both arms, if a change in antiretroviral therapy is indicated, the appropriate Trials Unit should be contacted. If simplification of the ART regimen is deemed necessary for clinical reasons during follow-up, this may be allowed, but must be discussed with the appropriate Trials Unit. **Switching of all drugs in the current ART regimen should only occur if there is immunological, virological or clinical failure (according to local clinical practice)**, at which point a new regimen should be chosen, this applies for the SCT arm who should re-start continuous therapy in this situation. Resistance tests or TDM may be used to inform change of regimen, according to local clinical practice.

Hypersensitivity reactions with ABC rarely occur after the first 6 weeks of therapy. However if the participant has a suspected hypersensitivity reaction and ABC is stopped (as per standard guidelines), rechallenge with ABC should NEVER take place. If therapy with ABC has been discontinued for any reason and restarting therapy is under consideration, the reason for discontinuation must be established to assess whether the patient had any symptoms of a hypersensitivity reaction. If a hypersensitivity reaction cannot be excluded, ABC must not be restarted. However restarting ABC after a scheduled SCT break is safe.

All other drugs should be modified (if required) as per standard clinical practice.

### **7.11 Non-trial treatment**

No concomitant medication for an acute illness should be taken at the time of study enrolment. Medication required for a concurrent illness during the study should be documented on the appropriate form.

### **7.12 End of trial**

Stable and virologically suppressed young people who were randomised to SCT can continue SCT after completion of the main trial if agreed by the clinician and family at least until the results of the main trial become available. 12-16 weekly HIV-1 RNA viral load monitoring will be funded by the PENTA Foundation where this is not local standard of care. Management of HIV-1 RNA viral load should continue as specified in appendix 15.

The trial will be considered to have ended once all participants have had their final long term follow up visits. See section Trial Closure 8.11.

## **8 ASSESSMENTS AND FOLLOW-UP**

Complete details of local laboratory issues and logistics are given in the Manual of Operations. Please also refer to flow sheets 1.9, 1.10, 1.11, 1.12 and 1.13 for the specific requirements at each visit.

### **8.1 Schedule for follow-up**

Participants being followed after week 48 should be seen every 12 weeks, until the last young person enrolled has completed 48 weeks of follow-up. Participants randomised to the SCT arm should continue to follow the SCT strategy until the end of the main trial unless the clinician or the family have concerns which they should discuss with the appropriate Trials Unit.

The clinician may request more frequent visits for participants in either arm, if required. The flowcharts (section 1.9, 1.10, 1.11, 1.12) indicate the minimum number of visits for protocol completion and data recording. However it is the investigator's responsibility to see participants as frequently as necessary, particularly for the monitoring of adverse events.

Participants should be fasting at week 0, 24 and 48 in order to obtain fasting lipids and glucose values.

### **8.2 Clinical examination**

A clinical examination must be performed at screening, randomisation and at identified follow-up protocol visits (see flowcharts 1.9, 1.10, 1.11, 1.12). At each visit the following should be recorded:

- Body weight and height
- All adverse events since last protocol visit, including in particular haematological abnormalities, pancreatitis, diarrhoea, clinical lipodystrophy, acute illnesses
- Change in HIV disease stage since last protocol visit

A physician assessment of lipodystrophy assessment should be performed at week 0 and repeated every 24 weeks until the end of the study. Tanner scales should also be completed at these time-points (Appendix 10).

Pregnancy tests should be performed for all females of childbearing potential at screening (week -4 to -2) and repeated every 24 weeks until the end of the trial and at other time-points if required. The pregnancy test at screening must be done within 72 hours of enrolment and its results must be received before randomisation. The pregnancy test can be either a urine sample or blood sample test. If a pregnancy test performed during the trial is positive please contact and discuss with the appropriate Trials Unit.

Ethnic origin data will be collected because it is known that ethnicity is a factor in the concentration levels of efavirenz [39].

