| Plasma storage f                       | X                     | X                  | X | X   | X   | X   | X  | Every 12 weeks                | X                  |
| Cell storage f                         | X                     | X                  | X | X   | X   |     | X  | Every 24 weeks                | X                  |
| Adherence questionnaire                           | X                     |                    | X | X   | X   | X   | X  | Every 12 weeks                | X                  |
| Acceptability Questionnaire                       |                       | X                  |   |     |     |     |    | If re-start continuous
ART | X                  |
| PedsQL™ Questionnaire                             |                       | X                  |   |     | X   |     | X  | Every 24 weeks                | X                  |

Notes: shaded boxes indicate visits where overnight fasting is required for blood lipids/glucose.

(X) – Indicates optional investigations.

*If insufficient blood is drawn, priorities are: local HIV-1 RNA, T cell subsets, plasma store, lipids/glucose, biochemistry, haematology*

(a) Clinical assessment: including height & weight (adjust doses), presence of adverse events and change in HIV disease stage (including clinical lipodystrophy).

(b) Biochemistry: Creatinine, Bilirubin, ALT, AST, Alkaline Phosphatase and Albumin. Calcium and Phosphate at baseline and annually thereafter.

(c) Haematology: Hb, MCV, WBC, Lymphocytes, Neutrophils, Platelets

(d) Lipids/Glucose: Triglycerides, Cholesterol (Total, HDL, LDL, VLDL), Glucose. Overnight fasting required at randomisation and weeks 24 and 48 and then every 48 weeks.

(e) Pregnancy Test: either a blood or urine sample. This test will be performed for all females of childbearing potential at screening and weeks 24 and 48 (then every 24 weeks) and at other time-points if required. The initial pregnancy test must be done within 72 hours of enrolment and its results must be received before randomisation.

(f) 16ml total blood draw for plasma and cell storage: 6.0ml in EDTA if plasma store only. [see Manual of Operations for instructions for plasma and cell handling and storage].

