## **5.2 Exclusion criteria**

- Pregnancy or risk of pregnancy in females of child bearing potential.
- Acute illness (young people may be enrolled after illness).
- Receiving concomitant therapy for an acute illness (young people may be enrolled after finishing therapy).
- A creatinine, AST or ALT of grade 3 or above at screening.
- On a regimen including nevirapine or a boosted PI (young people may switch to an EFV based regimen).
- Previous ART monotherapy (except for the prevention of mother-to-child transmission)

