#### 6.1.2 Investigations at screening visit

Randomisation (week 0) should take place no more than four weeks after the screening visit and ideally as soon as possible after eligibility has been confirmed. At the screening visit a trial number will be assigned and used on all paperwork and labels. A clinical assessment should be completed and the participant and/or carer should complete an adherence questionnaire according to age and knowledge of HIV diagnosis (see flow sheets 1.9, 1.10, 1.11 and 1.12).

Blood will be taken for haematological and biochemical investigations, T cell subsets (including RO/RA phenotype if available), measurement of HIV-1 RNA viral load (the same assay should be used at least throughout the pilot phase and ideally throughout the whole trial, although the assays used may vary across centres according to clinical practice and management), and for plasma and cell storage (if the participant attends a clinical centre where this is possible).

As soon as the biochemistry and immunological/virological results are received and eligibility has been confirmed, the screening form with confirmation of eligibility and receipt of informed consent, clinical history and assessment, haematology, biochemistry and HIV-1 RNA viral load should be faxed to the appropriate Trials Unit.

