## 6.2 Week 0 visit and randomisation procedure

### 6.2.1 All participants

The eligibility criteria and consent should be re-confirmed verbally and noted on the Randomisation Form. If the parents/carers and/or participant are prepared for Short Cycle Therapy to commence at this visit, contact the appropriate Trials Unit to enrol the participant (see General Information, 'Randomisations & SAE notifications' section at the front of the protocol for telephone and fax numbers). The Trials Units will inform the sites of the young person's allocation immediately (continuous ART or Short Cycle Therapy 5-on / 2-off strategy), which should be entered on the trial register.

A clinical assessment should be completed which will include measurements of height, weight, presence of adverse events, change in HIV disease stage and ethnic origin. The following investigations are to be performed: haematology, biochemistry, glucose and lipid profile (fasting), T cell subsets (plus RO/RA phenotype if available). Blood should be taken for plasma storage (plus cell storage if the participant attends a clinical centre where this procedure is possible or where a courier can be arranged). A quality of life questionnaire (PedsQL™) should be completed for all participants (and carers) and an acceptability questionnaire for those young people randomised to SCT (and carers) (see flow sheets 1.9, 1.10, 1.11 and 1.12). Participants should be given a diary to record when they have taken their ART, which will include a reminder to re-start therapy after the 2 days off ART in the SCT arm (Appendix 7). The diary will be anonymised by the clinical centre staff before being sent to the Trials Units.

For further details on specific requirements for the week 0 visit and randomisation procedures see sections 7.1, 7.3 and 7.6.

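### The pregnancy test that applies the 5.2 exclusion is tied to an undefined 'enrolment', so it either misses its own 72-hour limit or can be up to 28 days old at randomisation

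*Combined protocol and SAP*

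**What the plan says.** Section 5.2 excludes "Pregnancy or risk of pregnancy in females of child bearing potential". Section 8.2 schedules the test "at screening (week -4 to -2) and repeated every 24 weeks until the end of the trial and at other time-points if required", and then adds: "The pregnancy test at screening must be done within 72 hours of enrolment and its results must be received before randomisation".

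Note (e) under flowsheets 1.9 to 1.12 repeats the 72-hour rule and gives the schedule as "at screening and weeks 24 and 48 (then every 24 weeks) and at other time-points if required". Up to week 48, the pregnancy-test row in all four flowsheets is marked at screening, week 24 and week 48. The cells for randomisation, week 4 and week 12 are empty.

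On the gap between the two visits, section 6.1.2 says "Randomisation (week 0) should take place no more than four weeks after the screening visit" and prefers it sooner once eligibility is confirmed. Section 7.3 says much the same for the main trial. Section 7.1 asks pilot participants to attend for randomisation 2 to 4 weeks after screening.

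At the week 0 visit, section 6.2.1 has eligibility re-confirmed verbally and tells the site to "contact the appropriate Trials Unit to enrol the participant". Its list of week 0 investigations contains no pregnancy test. Section 6.1.1, on enrolment and consent, sits under the heading for screening procedures. The glossary has no entry for enrolment.

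**The concern.** The 72-hour limit is there to make the result current when it is used, but the event it is counted from can be read in two ways. On one reading the schedule cannot satisfy the rule. On the other the rule is satisfied but says nothing about how recent the result is when the exclusion takes effect, at randomisation. No passage requires a test close to randomisation on both readings.

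What is at stake is correct application of a stated exclusion and the safety of the participant. Section 10.2 instructs that a participant who becomes pregnant on SCT goes back to continuous therapy, and pregnancies are reported on an SAE form. Neither provision can operate on a pregnancy that nobody knows about.

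**Working it through.** The plan gives no statistical figure to reproduce here; the check is interval arithmetic on its own schedule.

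**Inputs**
- Limit: 72 hours = 3 days (8.2; note (e)).
- Scheduled test: week -4 to -2 = 28 to 14 days before week 0 (8.2; flowsheets).
- Longest permitted gap from screening to randomisation: 4 weeks = 28 days (6.1.2, 7.3). The main-trial text states no minimum; the pilot text says 2 to 4 weeks (7.1).
- Next scheduled test: week 24.

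**Reading A: enrolment is the week 0 act (6.2.1)**
- Gap in hours: 14 × 24 = 336; 28 × 24 = 672.
- Ratio to the limit: 336/72 = 4.7; 672/72 = 9.3.
- Excess in days: 14 − 3 = 11; 28 − 3 = 25.

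A test taken in the flowsheet window misses the limit by 11 to 25 days. A site complies only by doing a test that the flowsheets do not schedule, or by screening within 3 days of randomisation, which lies outside the flowsheet window.

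**Reading B: enrolment is at screening (6.1.1)**
- Gap from test to enrolment: about 0, so the limit is met.
- Age of the result at randomisation: 14 to 28 days in the pilot, 0 to 28 days in the main trial.

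**Time to the next scheduled test, on either reading**
- From a test in the flowsheet window: 24 + 2 = 26 weeks to 24 + 4 = 28 weeks.
- If a main-trial participant is randomised immediately after screening: 24 + 0 = 24 weeks.

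**Illustrative size.** The documents give neither the number of females of childbearing potential nor a conception rate. Assume 50 to 80 such participants and a 0.5% to 2% chance of conception per 28 days:
- Low: 50 × 0.005 = 0.25 participants.
- High: 80 × 0.02 = 1.6 participants.
- In the SCT arm at 1:1 allocation: about 0.13 to 0.8.

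At the high end, 0.8 out of 80 in the SCT arm is 1 percentage point. That is the most the arm's suppression rate could move, and only if every such participant's outcome changed; the non-inferiority margin is 12 points. Pregnancy is not a component of the primary outcome, so the realistic effect is smaller still.

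**The case against.** The strongest reply is that the text can be read consistently. The 72-hour sentence names enrolment and randomisation as separate events and concerns a test at screening. Section 6.1.1 puts enrolment under screening, and section 6.1.2 assigns the trial number there. On that reading 8.2, note (e) and the flowsheets agree. This stands to the extent that the text is ambiguous rather than necessarily self-contradictory. It does not settle the matter, because 6.2.1 enrols the participant at week 0 and 7.1 speaks of delaying enrolment when it means delaying randomisation. It also leaves the result up to 28 days old.

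A reader might infer that every eligibility test breaches the limit five- to nine-fold. The documents do not support that: the multiple holds only on Reading A and within the flowsheet window, and in the main trial the gap may be short. A reader might also infer that nobody can be retested before week 24. In fact additional tests are permitted, and the flowsheets are described as a minimum (1.5, 8.1). They are discretionary, however, so 'no test scheduled before week 24' is the accurate statement.

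The exclusion also covers risk of pregnancy, and a clinical assessment takes place at week 0. Both lower the chance of a missed case; neither replaces a test.

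Finally, the current version is dated May 2015, and the amendment log has recruitment running to the end of June 2013. On those dates a change to the entry schedule would not alter who entered this trial. That limits the practical effect, but the inconsistency remains in the current text.

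**Conclusion.** The point holds as a scheduling and definition gap. The test that applies the pregnancy exclusion either cannot meet the 72-hour rule as scheduled (Reading A, 11 to 25 days over), or meets it while being up to 28 days old at randomisation (Reading B). With no week 0 test scheduled and the next at week 24, an excluded participant could be randomised undetected.

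The size is small. The illustrative 0.25 to 1.6 participants rests wholly on assumed inputs, and the conclusion about the text does not depend on it. It would be tempting to go on to say that sites would admit different populations, or that early returns to continuous therapy in the SCT arm would distort the comparison. At fewer than two participants across the trial, analysed as randomised (11.6), neither follows. Conceptions after week 0 are also a separate matter: they face the same wait for the week 24 test however the entry test is timed.

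**What to change.** Reconcile sections 6.1.1, 6.2.1 and 8.2, note (e) and flowsheets 1.9 to 1.12:

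1. Define enrolment once and use the word in that sense throughout.
2. Time the test that applies the 5.2 exclusion against randomisation, keeping the protocol's own 72-hour limit and its requirement that the result be in hand first.
3. List that test among the week 0 checks in 6.2.1 to be completed before the Trials Unit is called, and mark it accordingly in the flowsheets.

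Whether a screening test is kept as well is for the sponsor to decide.

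The cost is a wording and flowsheet amendment. A urine test is already acceptable under 8.2. If the test is moved, an occasional screening visit is wasted because a positive result is found later; if it is added, one urine test is repeated.

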### 8.3 Antiretroviral therapy

Prescriptions of antiretroviral therapy and any alterations to prescribed doses should be recorded on the CRF. Doses should be checked at every visit and adjusted for body surface area, or weight as appropriate.

### 8.4 Laboratory tests

Laboratory tests for efficacy and safety monitoring will include:

|                     |                                                                                                                                                                                                               |
|---------------------|---------------------------------------------------------------------------------------------------------------------------------------------------------------------------------------------------------------|
| Haematology:        | Haemoglobin, MCV, platelets
white cell count, neutrophil and lymphocyte counts                                                                                                                             |
| Biochemistry:       | Creatinine, albumin, total bilirubin, ALT (SGOT), AST (SGPT),
alkaline phosphatase, calcium, phosphate.                                                                                                    |
| Lipids/glucose:     | Triglycerides, cholesterol (total, LDL, HDL, VLDL), glucose
(participants should be fasting overnight at randomisation, weeks 24 & 48
and then every 48 weeks during the main trial) |
| Lymphocyte subsets: | CD3 (absolute and percentage)
CD3+CD4 (absolute and percentage*)
CD3+CD8 (absolute and percentage*)
Total lymphocyte count (if measured by immunology laboratory)
* including RA/RO phenotype     |
| Virology:           | HIV-1 RNA (viral load) using an ultrasensitive assay. It is also
planned to do resistance testing on stored samples.                                                                                       |

### 8.5 Cells and Plasma for storage

6ml of EDTA blood will be collected throughout the trial for plasma storage for viral load testing and analyses as part of the virology/immunology substudy (Appendix 11), and other HIV related tests as appropriate. Plasma will be stored at weeks -4 to -2 (screening), week 0 (randomisation), 4, 8 (pilot only), 12, 24, 36 and 48 from all participants in both arms. Plasma will also be stored at weeks 1, 2 and 3 for participants in the pilot phase. (See flowsheets)

In addition, in centres who have capability, cells from all participants will be stored at weeks -4/-2 (screening), 0, 4, 12, 24, 48 and every 24 weeks until the end of the trial at  $-80^{\circ}\text{C}$  for subsequent assessments as part of the virology/immunology substudy (see Appendix 11). An extra 10ml of whole blood is required at the time points for cell storage.

## **8.6 Adherence and acceptability**

All carers and children, where appropriate, will be asked to complete adherence and acceptability questionnaires in accordance with flow charts 1.9, 1.10, and 1.11.

Adherence and acceptability questionnaires should be completed without conferring with friends or relatives and all questions should be answered even if the carer/young person feels them to be irrelevant. The appointed person at the site should check each questionnaire for its completeness, ensuring that the correct date of completion and patient identifiers are present. The Research Nurse should approach young people at appropriate clinical visits to complete a questionnaire.

For children unaware of their diagnosis or not deemed to be sufficiently competent by the paediatrician, the parents or carer should complete a questionnaire on behalf of the child.

## **8.7 Measures of adherence**

Close monitoring of viral load is likely to rapidly identify non-adherence to ART in both arms. Additionally each participant and/or caregivers (as appropriate depending on age and knowledge of HIV diagnosis) should complete an adherence questionnaire at weeks -2, 4, 12, 24, 36 and 48.

Adherence to strategy could be affected if the young people recruited to the SCT arm decide to extend the permitted weekend-only interruptions or forget to stop taking the medication on the days off. To combat this potential issue, clinic staff will be instructed to stress the importance of keeping to the strategy within the trial. Additionally the patients/parents/carers (as appropriate) will complete a diary which will assist in reminding participants to re-start therapy after the 2 days off ART (Appendix 7). Participants in the continuous ART arm will also complete a diary to look at adherence to their ART regimen 7 days a week.

Clinical teams may organise for text message reminders to be sent to participants' mobile to assist with adherence. This should only be done if the participant thinks this will be beneficial and agrees to this.

Further adherence measures include using MEMS cap. For further details see section 1.7.3.

## **8.8 Measures of acceptability of treatment strategy and quality of life**

Participants randomised to the SCT arm (as appropriate depending on age and knowledge of HIV diagnosis) should complete a self-administered acceptability questionnaire at randomisation (week 0) and at the final visit if following the SCT strategy, or at the re-start of continuous therapy. Where a parent/carer is involved, they should complete the relevant questionnaire.

Quality of life (PedsQLTM) questionnaires should be completed by all participants (regardless of which arm they are in) at randomisation (week 0) and then every 24 weeks.

